## Discussion

In diabetes self-management education the ‘one-size-fits-all’ approach is not very effective. Not all patients will possess the necessary self-management skills. While a certain motivation and perseverance may be needed to change one’s behaviours, successful maintenance ultimately depends on one’s ability to anticipate and deal with a wide range of potential stressors that challenge diabetes management and long-term health. This is the central tenet of proactive coping, a self-regulatory model which describes the steps people take in pursuit of their long-term goals. From our previous research we know that proactive coping may be a better predictor of good long-term self-management than either intentions or self-efficacy [18]. The current study will add knowledge about the program in three different aspects: its 2.5 year (cost-) effectiveness and the impact of pre-selection of patients. This knowledge will be of importance, because to deal with the global diabetes epidemic, cost-effective self-management education programs that are also effective on the long run are needed.

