**Conclusions:**

By differentiating between patients who will and those who are likely not to benefit from the educational program, a more (cost-) effective self-management program might be designed, also on the long-run.

*Trial registration* NTR 5330

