Group based educational programs for diabetes self-management can improve blood glucose, blood pressure, body mass index (BMI) and the requirement of blood glucose lowering drugs; however, the long-term results were varying [4]. In Italy, non-insulin-treated T2DM patients known with diabetes for at least 1 year were randomised to either group or individual care in a hospital-based setting. After 4 years clinical, cognitive, and psychological outcomes were better in the group based treatment [5]. In the DESMOND trial, greater improvements in weight loss and smoking cessation were found in the intervention group at 1-year-follow-up, but at 3-year-follow-up this effect was no longer apparent [6, 7]. In general, completers of a diabetes self-management intervention study are significantly more highly educated than dropouts [8]. This indicates that interventions to improve self-management should be tailored to different categories of patients. The ‘one size fits all’ principle in diabetes education research is outdated. To estimate a priori the chance of successful self-management of a patient, the self-management screening tool (SeMaS) can be used [9]. With SeMaS possible barriers for self-management due to depression and/or anxiety can be detected. Both depression and anxiety can interfere with the effectiveness of a self-management program at that moment for a particular person and should be dealt with before following the program. Besides, individuals with already high self-management capabilities are likely to have no additional benefit from an educational course [10–12].

We hypothesise that by differentiating between patients who may and those who may not benefit from a self-management program, a more (cost-) effective self-management education program can be designed which is also effective on the long-run. Therefore, the aim of the current study is to investigate the cost-effectiveness and long-term effects of the educational program BGI on cardiovascular risk, quality of life and diabetes self-management behaviour in a preselected group of known T2DM patients.

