### Pre-selection

The pre-selection procedure to assess a patient’s capabilities of self-management will be performed with the use of the SeMaS, a self-management screening tool which is validated in T2DM patients and sent to the patients home [9]. The SeMaS is a 27 item questionnaire covering self-management abilities of five psychosocial domains [locus-of-control (3 items), self-efficacy (2 items), social support (1 items), coping (9 items), anxiety (4 items) and depression (3 items)], three skills items (computer, group and self-care) and two other items including perceived burden of disease [9]. All separate items range from 0 to 3 on a 4-point Likert scale (locus-of-control, self-efficacy, coping, skills items) or from 0 to 2 on a 3-point Likert scale (social support, anxiety, depression). For all items higher scores represent higher capability, except for those in the anxiety and depression domain where higher score represent more barriers. The perceived burden of disease is scored on a visual analogue scale from 0 to 10. Patients with high scores on the domains anxiety (score >4 from total 8) and/or depression (score >3 of total 6) will be excluded during the pre-selection. Those patients first need to deal with their mood disturbance before they are able to improve their self-management skills. Patients without barriers for self-management, so with maximal self-management capacity (highest possible scores for the locus-of-control, self-efficacy, social support, coping and for anxiety ≤4 and for depression ≤3) were also excluded, since they would not benefit from the educational course. The general practitioner (GP) will be informed about the SeMaS scores of all participants.

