### Randomisation

Patients who are eligible after the pre-selection will be randomised (1:1) based on computer-generated random numbers, with sealed, opaque, sequentially numbered allocation envelopes. All patients entering the trial receive a random number from the coordinating research centre (Julius Center). Each number corresponds to either ‘BGI course’ (BGI-group) or ‘no BGI course’ (control-group). As patients will attend a course in the intervention group, it is not possible to blind participants for the treatment allocation. Patients from the same practices and general practitioners will attend a different course, so no large cluster-effect is expected.

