### Control group

As stated above, participants in the control group will receive similar diabetes care as those in the intervention group, according to the guidelines of the Dutch College of General Practitioners [16]. The only difference between both groups will be the additional BGI course.

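### The Discussion promises knowledge on the impact of pre-selection, but no contrast in the trial can estimate it

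*Protocol article*

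**What the plan says.** All references are to the protocol article.

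- **Discussion.** Among the contributions the study will make, it names "its 2.5 year (cost-) effectiveness and the impact of pre-selection of patients". The sentence carries no hedge.
- **Background, hypothesis.** "We hypothesise that by differentiating between patients who may and those who may not benefit from a self-management program", a program that is more (cost-)effective, and still so in the long term, can be designed.
- **Background, aim.** The next sentence is narrower: long-term effects and cost-effectiveness of BGI "in a preselected group of known T2DM patients".
- **Pre-selection.** Patients scoring above 4 of 8 on anxiety and/or above 3 of 6 on depression "will be excluded during the pre-selection". Those with maximal self-management capacity are removed too.
- **Randomisation.** "Patients who are eligible after the pre-selection will be randomised (1:1").
- **Control group.** "The only difference between both groups will be the additional BGI course".

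**The concern.** The hypothesis and the promised contribution concern pre-selection as a strategy. The randomised comparison concerns the BGI course among people who have already been selected. These are different questions, and the second does not answer the first.

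What is at stake is interpretation. With the present wording, a favourable result could be taken as support for SeMaS selection and an unfavourable one as evidence against it. Neither reading would follow from the data. The point matters in practice because selection decides who is offered the course.

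**Working it through.** **1. What the impact of pre-selection would be.** Write D_S for the effect of BGI against usual care in patients who pass the screen, D_X for the effect in those screened out, and p for the proportion who pass.

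- Average effect if BGI were offered without selection: p·D_S + (1 − p)·D_X.
- Gain in average effect from selecting: D_S − [p·D_S + (1 − p)·D_X] = (1 − p)·(D_S − D_X).

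Estimating the gain needs both D_S and D_X.

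**2. What the trial supplies.**

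| Element | Where | Bears on |
|---|---|---|
| Allocation only after screening | Randomisation | D_S |
| Arms differ only in the course | Control group | D_S |
| BMI model with intervention and time-by-intervention terms | Statistical analyses | D_S |
| ICER of BGI versus control | Cost-effectiveness | D_S, in costs and QALYs |
| Characteristics of participants and non-participants | Statistical analyses | neither effect |

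Nothing bears on D_X. Both arms were screened, so the ICER does not evaluate screening as a strategy either.

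**3. What the sample size is for.** Inputs from Sample size: difference 0.77, SD 1.7, 6 measurements, AR(1) correlation 0.70, alpha 0.05 (two-sided assumed, as sidedness is not stated), power 80%.

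- Sum of the 6 × 6 correlation matrix: 6 + 2·(5·0.7 + 4·0.49 + 3·0.343 + 2·0.2401 + 0.16807) = 20.27.
- SD of the six-measurement mean: 1.7·√(20.27/36) = 1.276.
- n per group: 2·(1.960 + 0.842)²·1.276²/0.77² = 43.1, rounded up to 44.

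This reproduces the stated 44 per group (power 80.8% at 44). The calculation sizes one contrast, BGI against control in selected patients. No arm or stratum is assigned to pre-selection.

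**4. Whether the earlier BGI study can stand in for D_X.** Primary outcome measure keeps the same outcome to allow comparison with that study.

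| | Earlier study | This trial |
|---|---|---|
| Population | screen-detected type 2 diabetes | diagnosed 3 months to 5 years ago |
| Follow-up | 9 months | 2.5 years (30 months) |
| SeMaS pre-selection | presented as new in this trial | yes |

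Three features change together, so a difference in effect between the studies cannot be assigned to any one of them.

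**The case against.** The strongest reply is that the formal aim, in both the Abstract and the Background, is already confined to a pre-selected group. The primary outcome, sample size, analysis and ICER all serve that aim. This stands: the trial is coherent on its own question, and the fault lies in the hypothesis and the Discussion. It does not remove the point, because the Discussion claim is unhedged and wider than the aim.

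A reader might infer more than the document supports in five ways:

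- **That the Abstract makes the same error.** Its conclusion opens "By differentiating between patients who will and those who are likely not to benefit from the educational program", but says only that a better program might be designed. That is hedged rationale.
- **That the trial should test its own exclusion rule.** Pre-selection says that patients with maximal capacity "were also excluded, since they would not benefit from the educational course". This gives the reason for an eligibility criterion, and a trial need not test its criteria.
- **That excluded patients have no outcome data.** The article does not say so. Consent precedes screening (Recruitment) and clinical measures come from GP records (Clinical measures), so routine data could exist. They would still give no BGI effect, because these patients are not randomised.
- **That the investigators plan to credit the result to selection.** No such analysis is described. The misreading is a risk created by the wording.
- **That an arm-by-SeMaS interaction among randomised patients would repair the gap.** SeMaS is described by separate domain scores, so a single interaction is undefined. It would cover only the range left after exclusion and would say nothing direct about the patients removed.

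A separate analysis plan may exist, but it cannot recover an effect in patients who were never allocated.

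**Conclusion.** The point holds in a limited form. The article promises knowledge on the impact of pre-selection and builds its hypothesis on it, but the design identifies only the effect of BGI within SeMaS-selected patients. The gap is one of identification, so no sample size closes it. The comparison of BGI with usual care in selected patients is unaffected and agrees with the formal aim.

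The conclusion rests on the article's own account that allocation follows screening and that the arms differ only in the course. It needs no assumption about whether excluded patients would benefit. It is a correction to what the trial may conclude and should be made, but it does not threaten the primary analysis.

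**What to change.** 1. In the Discussion, remove the impact of pre-selection from the list of contributions.
2. In the Background, restate the hypothesis to match the aim: BGI added to usual care improves 2.5-year outcomes and is cost-effective in a SeMaS-selected population with known type 2 diabetes.
3. Add one sentence saying that the results will not be interpreted as evidence for or against pre-selection, including through comparison with the earlier BGI study.

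The cost is wording and a narrower claim. No arm, endpoint, sample size or analysis changes, and no interaction model is needed.

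Keeping the wider claim would require randomising unselected or screened-out patients, which is a different trial. As an illustration on assumptions not in the article (four equal cells, effective SD 1.276, two-sided 0.05, 80% power), the number per cell is 4·1.276²·(1.960 + 0.842)²/d². A difference in effect of d = 0.77 between strata needs 87 per cell, or 348 completers. Half of that, d = 0.385, needs 345 per cell, or 1,380. The planned enrolment is 106.

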## Abbreviations

ADDQoL: Audit of Diabetes-Dependent Quality of Life
BGI: beyond good intentions
BMI: body mass index
CVD: cardio vascular disease
EQ-5D: Euro QoL 5D
EQ-VAS: Euro QoL visual analog scale
DOH: De Ondernemende Huisarts
QALY: quality-adjusted life years
PASE: physical activity scale for elderly
PDMI: proactive diabetes management inventory
PoZoB: Praktijkondersteuning Zuidoost Braband
SDSCA: summary of diabetes self-care activities measure
SeMaS: self-management screening tool
SF-36: short-form 36
SGE: Stichting Gezondheidscentra Eindhoven
T2DM: type 2 diabetes mellitus
